### Inclusion criteria

2.5

Meets diagnostic criteria for hypertension and chronic heart failure (3, 10), with left ventricular ejection fraction (LVEF) ≤ 40% and serum NT-proBNP ≥450 pg/mL; Before randomization, participants must have clinically stable symptoms and comorbidities, patients with recent worsening heart failure or hospitalization may be screened only after clinical stabilization.Meet the syndrome criteria for toxic-pathogenic syndrome in CM (https://www.cacm.org.cn/2024/12/02/30894/);Age 18–75 years, no gender restrictions;NYHA functional class II–III;Voluntary participation with understanding and signed informed consent.

### Exclusion criteria

2.6

Acute myocardial infarction (within 14 days);Concurrent severe hepatic impairment (ALT > 100 U/L or AST > 100 U/L), severe renal impairment (glomerular filtration rate < 30 mL/min), or severe electrolyte imbalance (serum potassium > 5.5 mmol/L or < 3.5 mmol/L);Severe hematologic disorders or malignancies;Pregnancy or lactation;Patients with psychiatric disorders;Patients with severe heart failure and a life expectancy of less than six months;Patients who have taken other Chinese herbal medicines or proprietary Chinese medicines with similar functions or components to the investigational drug within the past month;Patients with known adverse reactions or allergies to the study drug;Patients who have participated in other drug clinical studies within one month prior to enrollment.

### Exit criteria

2.7

All subjects who have completed the informed consent form and been screened as eligible for the trial will not have their subsequent treatment affected regardless of when or why they withdraw. Patients have the right to withdraw from the study at any time and for any reason; however, unnecessary withdrawals should be minimized, and proactive measures should be taken to complete follow-up whenever possible to facilitate analysis of efficacy and safety. When a patient decides to withdraw, the investigator should contact the patient or their responsible relative via telephone or in-person visit to confirm the reason for withdrawal whenever possible. The investigator should collect any remaining medication upon withdrawal, complete the final assessment, finalize the case report, explain the reason for withdrawal, and follow up on any endpoint events occurring in the withdrawn patient. If the reason for withdrawal is an adverse event, it should be documented in the CRF.

### Termination criteria

2.8

Treatment with the study drug may be discontinued under the following circumstances: (1) The patient may discontinue treatment at any time; (2) An allergic reaction clearly attributable to the study drug occurs; (3) Adverse symptoms or signs, or abnormal test results clearly attributable to the study drug occur, leading to a determination that discontinuation is necessary; (4) A woman of childbearing potential becomes pregnant during the study period.

The entire trial may be terminated at all sites if any of the following issues arise during the study: (1) The investigator identifies a serious safety concern; (2) A major protocol deviation occurs; (3) The sponsor discontinues funding or management support; (4) The regulatory authority withdraws approval for the trial.

### Randomized design and blind method

2.9

This study employed stratified block randomization, with research centers as the stratification factor. The randomization table was generated by a statistician not involved in the study's statistical analysis using the PLAN procedure in SAS software. Samples were assigned according to group codes at a 1:1 ratio (Group A:Group B). Parameters such as block length and initial seed number, along with the randomization table itself, served as the primary blinding mechanism. The treatment assignments (experimental group, control group) corresponding to each group code constituted the secondary blinding mechanism. Both primary and secondary blinding layers were prepared in duplicate, sealed in opaque envelopes, and stored separately at the study coordinating institution and the sponsor. After screening and eligibility confirmation at each center, subjects were assigned random numbers sequentially based on enrollment timing and the center's allocated random number range. Medication corresponding to the assigned random number was then dispensed.

This study employs a double-blind design, meaning investigators, subjects, and all trial personnel remain blinded throughout the clinical trial. On-site drug blinding is guided by personnel from a statistical unit not involved in this study. The sponsor arranges for individuals unrelated to this trial to affix the pre-assigned drug codes onto labels. After packaging, each subject's medication will bear a unique drug code label corresponding to the drug code in the randomization table, which remains unchanged throughout the trial. Blinding records are maintained throughout the blinding process.

### Treatment

2.10

After randomization, the treatment group received QSG, while the control group received a placebo version of QSG (2 sachets per dose, 5 g per sachet, twice daily, taken 30 min after breakfast and dinner respectively, dissolved in 150 mL of boiling water at 100 °C and stirred thoroughly). All participants received standardized treatment according to the Chinese Hypertension Prevention and Treatment Guidelines (2018 Revised Edition) (10)and the AHA/ACC/HFSA Heart Failure Management Guidelines 2022 (3). Unless contraindicated or not tolerated, the regimen will include the four foundational HFrEF drug classes: a renin–angiotensin system inhibitor, an evidence-based beta-blocker, a mineralocorticoid receptor antagonist, and an SGLT2 inhibitor. Antihypertensive treatment will follow the guidelines. Drug selection and doses will be individualized toward guideline-recommended target doses or the participant's maximum tolerated doses before enrollment. During the 12-week treatment period, investigators will aim to keep drug classes and doses stable. Any clinically necessary initiation, discontinuation or dose change, together with the date, reason and new dose, will be recorded in the CRF. Concomitant-medication exposure and major treatment changes will be summarized by group and evaluated in sensitivity analyses.

### Storage and management of medications

2.11

Investigational medicinal products shall be stored under lock and key in a secure, controlled indoor area, protected from moisture. Each trial site must designate a responsible person for the management and storage of investigational medicinal products. Each time the investigator dispenses medication to a subject during a follow-up visit, the Medication Dispense Record must be completed, accurately and promptly recording the quantity dispensed and reminding the subject to return any remaining medication at their next visit. The quantity of returned medication shall be collected and verified, with the details recorded in the Medication Dispense/Return Record. At trial completion, all remaining medication must be returned to the sponsor with a completed Investigational Medicinal Product Recovery Form. Undistributed medication must be returned in its original sealed packaging. Remaining medication after trial completion shall be collected by the monitor for centralized disposal.

### Outcome indicators

2.12

#### Primary outcome

2.12.1

The main primary outcome is the NT-proBNP responder rate at week 12, defined as a decrease in NT-proBNP exceeding 30% from baseline. Collect fasting plasma from subjects and measure NT-proBNP levels following the reference kit protocol. The six-minute walk test assessed exercise tolerance by having patients walk as far as possible on a flat corridor within 6 min. Distances were categorized as: <150 m: Severe heart failure; 150–450 m: Moderate heart failure; >450 m: Mild heart failure.

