**Methods:**

This is a multicenter, prospective, randomized, double-blind, placebo-controlled clinical trial. A total of 220 eligible participants with hypertension and HFrEF will be recruited and randomized in a 1:1 ratio to receive either QSG or placebo for 12 weeks. All participants received guideline-directed treatment for hypertension and HFrEF throughout the study period. The primary outcome is the improvement rate in plasma NT-proBNP levels from baseline to endpoint and the six-minute walk test. Secondary outcomes include echocardiographic parameters, NYHA functional class, Kansas City Cardiomyopathy Questionnaire (KCCQ), and Heart Failure Toxicity Scale. Safety measures, including liver and kidney function blood tests and adverse events, were used to assess QSG safety. We also conducted follow-up assessments at weeks 26 and 52 to evaluate patient readmission rates and the occurrence of cardiovascular adverse events.

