### Data analysis and statistical methods

2.15

SPSS 24.0 software will be used to perform statistical analysis on the collected data. All statistical tests will be two-tailed, with a *P*-value ≤ 0.05 indicating statistical significance for the tested difference. Descriptive analysis: Categorical indicators will describe the number and percentage of cases in each category. Quantitative indicators will be described using mean, standard deviation, maximum value, minimum value, median, lower quartile (Q1), and upper quartile (Q3). Comparisons between two groups of general characteristics will be analyzed using appropriate methods based on the type of indicator. For quantitative data, between-group comparisons will employ paired t-tests or Wilcoxon signed-rank tests. For categorical data, chi-square tests or exact probability methods will be used. For ordinal data, Wilcoxon signed-rank tests or the Mann–Whitney U (MWU) test will be applied. Age, atrial fibrillation status and estimated glomerular filtration rate will be recorded at baseline and examined in covariate-adjusted and sensitivity analyses because these factors can materially alter NT-proBNP concentrations. Time to first event will be displayed with Kaplan–Meier curves, compared by the log-rank test, and modeled using Cox regression to estimate hazard ratios (HRs) with 95% confidence intervals. Event counts and recurrent rehospitalizations will be summarized descriptively by group.

The Full Analysis Set (FAS) followed the intention-to-treat principle, including all randomized subjects who received at least one dose of the study drug, with exclusions limited to major protocol violations, no study drug exposure, or complete lack of post-randomization data. The per-protocol set (participants with ≥80% adherence, primary endpoint data and no major protocol violation) will support sensitivity analyses, and the safety set will include all randomized participants who received at least one dose and had a safety assessment. For missing co-primary endpoint data, the prespecified conservative worst-case approach will be used in the primary FAS analysis. Missing data amount, reasons and patterns will be reported by group. Multiple imputation under a missing-at-random assumption will be used as a sensitivity analysis, with additional best/worst-case analyses to evaluate departures from that assumption.

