## Discussion

3

HFrEF represents a severe manifestation or end-stage condition of various cardiac diseases (13). Long-term hypertension predisposes to pathological changes such as ventricular remodeling, leading to heart failure with reduced ejection fraction (14). Although ACEIs/ARBs, beta-blockers, and SGLT2 inhibitors have become cornerstones of standard HFrEF therapy, long-term patient outcomes remain suboptimal with persistently high readmission rates (15, 16). CM demonstrates favorable effects on long-term efficacy and readmission rates in heart failure, though individual responses vary considerably.

Based on CM theory, we integrate the primary symptom clusters of HErEF—restlessness, dyspnea, chest tightness, cold extremities, orthopnea, lethargy, edema, dry mouth with bitter taste, sallow complexion, jugular vein distension, cyanosis of lips and nails, palpitations, fatigue, oliguria, elevated high-sensitivity C-reactive protein (CRP), elevated interleukin (IL)-6, and elevated neutrophil-to-lymphocyte ratio (NLR) in patients with hypertension and HErEF. We propose a “toxic” state in these patients and developed the compound formula QSG with “Yiqi Jiedu” functions for heart failure treatment. Preliminary studies confirmed the efficacy and safety of QSG, but high-quality clinical evidence regarding its therapeutic effect in hypertension associated HFrEF remains lacking. Therefore, with support from the Ministry of Science and Technology, we conducted this multicenter, double-blind, randomized placebo-controlled trial to investigate the efficacy and safety of QSG in hypertension associated HFrEF patients.

The primary characteristic of HFrEF is reduced exercise tolerance resulting from impaired cardiac and vascular function. Dyspnea and fatigue are the main manifestations of exercise intolerance and also hallmark symptoms of HFrEF. This study employs the six-minute walk test as one of the primary outcome measures to objectively assess exercise tolerance in hypertension associated HFrEF patients. Additionally, we selected the change in NT-proBNP from baseline to the end of treatment as a key outcome indicator. As the most valuable and reliable laboratory biomarker for heart failure recommended by guidelines, NT-proBNP is characterized by ease of measurement, accuracy, and reproducibility (17, 18). It is commonly used to diagnose heart failure, stratify risk, and evaluate the clinical efficacy of medications.

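### The six-minute walk test is called a primary outcome, but the only form stated for it is three wide severity bands; distance in metres should be named as the analysed variable

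*Protocol article*

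**What the plan says.** Three places give the walk test primary status. The abstract states: "The primary outcome is the improvement rate in plasma NT-proBNP levels from baseline to endpoint and the six-minute walk test". The Discussion states: "This study employs the six-minute walk test as one of the primary outcome measures". Section 2.15 refers to more than one such endpoint: "For missing co-primary endpoint data, the prespecified conservative worst-case approach will be used in the primary FAS analysis".

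Section 2.12.1 describes how the test is performed and then gives the only form in which its result appears: "Distances were categorized as" one of three grades, severe below 150 m, moderate from 150 to 450 m and mild above 450 m. It states no change in metres, mean distance or walk-test responder rule, and attaches no time point to the walk test itself.

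Section 2.15 lists one set of tests for quantitative data and another for ordinal data, and assigns neither to the walk test. The covariates it names for adjusted analyses (age, atrial fibrillation, eGFR) are there because of NT-proBNP; baseline walk distance is not among them.

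NT-proBNP is handled differently. Its endpoint is explicit: "The main primary outcome is the NT-proBNP responder rate at week 12, defined as a decrease in NT-proBNP exceeding 30% from baseline". Section 2.3 gives a prognostic reason for the 30% cut and sizes the trial on it.

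**The concern.** Distance is measured in metres, but the middle band is 300 m wide (450 − 150). Eligibility is NYHA class II–III, so clustering in that band is plausible. A patient who improves by a few tens of metres registers on the band scale only when starting close to a cut. If the bands are the tested variable, a null walk-test result would say little about exercise tolerance.

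If the bands are not the tested variable, the text leaves open whether a primary outcome is analysed in metres or in categories. That choice should not be made after the data are seen.

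**Working it through.** **Evaluable numbers, from Section 2.3.** Inputs: 53% vs 33%, two-sided α = 0.05, power 0.80, 15% dropout.

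n per arm = (0.53×0.47 + 0.33×0.67) × (1.960 + 0.842)² / 0.20² = 0.4702 × 7.849 / 0.04 = 92.3, so 93. Then 93 / 0.85 = 109.4, so 110, which is the stated figure. The pooled-variance formula gives 96 and 113. I use 93 evaluable per arm. No figure is stated for the walk test.

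**Assumptions for walk distance (none is in the documents).** Baseline mean 300–400 m, SD 90–120 m at both visits, correlation 0.7 between baseline and week 12, normal distributions, no mean change on placebo and a 30 m gain on QSG.

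**Share starting in the middle band**, Φ((450 − mean)/SD) − Φ((150 − mean)/SD):
- Mean 300, SD 90: Φ(1.67) − Φ(−1.67) = 0.90
- Mean 320, SD 90: Φ(1.44) − Φ(−1.89) = 0.90
- Mean 400, SD 120: Φ(0.42) − Φ(−2.08) = 0.64

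**Share of QSG patients changing band by week 12 (simulation):** 13% at mean 300, SD 90, up to 27% at mean 400, SD 120.

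**Power in metres** (normal approximation, √(2/93) = 0.1466):
- Unadjusted, Φ(30/(SD × 0.1466) − 1.96): SD 90 gives Φ(0.31) = 0.62; SD 120 gives Φ(−0.26) = 0.40.
- Baseline-adjusted, residual SD = SD × √(1 − 0.7²) = 0.714 × SD: SD 90 gives Φ(1.22) = 0.89; SD 120 gives Φ(0.43) = 0.67. Simulation gives 65–89%.

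**Power on the bands** (simulated, Mann–Whitney on the week-12 band): about 27–37% over most of the range. The highest value is about 42–44% at mean 400 m, SD 90 m, where many patients sit near the 450 m cut.

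**Separating the two effects at mean 320 m, SD 90 m:**

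| Analysis | Power |
|---|---|
| Week-12 bands, Mann–Whitney | 30–34% |
| Week-12 bands, adjusted for baseline distance | 38–41% |
| Week-12 metres, unadjusted | 59–63% |
| Week-12 metres, ANCOVA on baseline | 88–89% |

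The ranges are from repeated simulations. Moving from bands to unadjusted metres accounts for roughly half of the distance from the first row to the last; baseline adjustment accounts for the rest. With adjustment on both sides, banding costs more: about 89% against about 40%.

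**Second parameterisation.** Fixing the SD of within-patient change at 70 m, with baseline mean 250–400 m, SD 80–120 m and a 30 m difference, power is 81–84% for change in metres, 21–33% for the week-12 band and 31–36% for change in band.

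**The case against.** The strongest reply is that Section 2.12.1 never says the bands are the tested variable. The sentence follows a description of the test and can be read as a key for interpreting distances. Section 2.15 plans means, SDs and tests for quantitative indicators, and distance is one. This is an article, and a fuller protocol or SAP may settle the matter.

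Much of this stands. A reader might infer that the trial is committed to the bands and that most patients cannot change category. The documents support neither: metres are measured, the analysed variable is not named, and under the assumptions above 13–27% of treated patients do change band. A reader might also ascribe the whole gap between about a third and 89% power to banding; about half of it comes from baseline adjustment.

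What does not stand is that this is only omitted detail. For an outcome it calls primary, the article prints one form, and it is a poor one. An analyst following the text could reasonably use it.

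A further tempting step is to fault NT-proBNP for being dichotomised, since the Discussion says "we selected the change in NT-proBNP from baseline to the end of treatment as a key outcome indicator". That does not hold. The responder rule, "defined as a decrease in NT-proBNP exceeding 30% from baseline", is defined, justified and the basis of a sample size that reproduces. A fall of more than 30% is itself a criterion on change. On a normal log scale, 53% vs 33% is a shift of 0.515 SD, and a continuous test would have about 94% power against about 79–80%. That loss is a deliberate choice the trial is sized for.

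**Conclusion.** The point holds in a limited form. The walk test has primary status, its only printed form is three bands with a 300 m middle, and the choice between metres and bands is not fixed. If the bands were analysed, the power to detect a 30 m gain would be well under one half in every scenario tried. Unadjusted metres would do better and baseline-adjusted metres better still.

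The direction held across all the means and SDs tried. The size depends on an assumed distance distribution, correlation and gain that the documents do not supply. Confidence is therefore moderate. This should be corrected, but it does not undermine the main NT-proBNP comparison.

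**What to change.** In Sections 2.12.1 and 2.15, before unblinding, name six-minute walk distance in metres at week 12 as the analysed variable. Compare the arms by ANCOVA with baseline distance and centre (the randomisation stratification factor) as covariates, and report the adjusted difference in metres with its 95% confidence interval. Keep the three bands as a descriptive shift table from baseline to week 12.

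The cost is wording only, because the distance is already measured. Leave the NT-proBNP responder rate as the main primary outcome. A baseline-adjusted analysis of log NT-proBNP could be added as optional support, at the cost of one more planned analysis; its absence is not an error.

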#### Secondary outcome

2.12.2

The following parameters were obtained via echocardiography: Left ventricular ejection fraction (LVEF), Left ventricular end-diastolic diameter (LVEDD), Left ventricular end-systolic diameter (LVESD), Interventricular septal thickness (IVS), Left ventricular posterior wall thickness (LVPW), Left ventricular short-axis fractional shortening (FS), Early diastolic peak mitral flow velocity/ late diastolic mitral flow peak (E/A), and early diastolic mitral flow velocity/tissue Doppler early diastolic annular velocity (E/e’).NYHA Functional Class: The NYHA classification categorizes the impairment of cardiac function into four levels based on the level of activity that induces heart failure symptoms (12).Kansas City Cardiomyopathy Quality of Life Questionnaire (KCCQ): KCCQ is a scoring tool used to assess the health status of patients with heart failure. It comprises 23 questions across seven domains: physical limitations, self-assessment, symptoms, self-awareness, psychological aspects, social functioning, and clinical assessment. Completion typically takes 4–6 min. Each question is scored out of 100 points, with higher scores indicating better quality of life.Quantification Table for Toxic Pathogenic Factors in Heart Failure (https://www.cacm.org.cn/2024/12/02/30894/).

#### Safety assessment

2.12.3

This trial will assess safety by monitoring adverse events (AEs), serious adverse events (SAEs), and discontinuation or treatment modifications due to AEs. Safety assessments at weeks 0, 4 and 12 will include vital signs, blood/urine/stool routine testing, 12-lead ECG, liver function, renal function, coagulation testing, and electrolytes including serum potassium and sodium; echocardiography and chest radiography are performed at weeks 0 and 12. All AEs will be graded from I (mild) to V (fatal), assessed for relationship to study treatment using the prespecified five-category causality scale, and followed until resolution, return to baseline or stabilization. SAEs will be reported to the monitor, coordinating center and manufacturer within 24 h. Independent monitors and auditors will oversee protocol adherence, source-data verification and safety reporting; this oversight is used instead of a separate data safety monitoring committee.

#### Long-term follow-up outcomes and event adjudication

2.12.4

At weeks 26 and 52, investigators will collect the number and dates of heart-failure rehospitalizations and major cardiovascular events through scheduled contact, participant/family interview and review of hospital source records. Heart-failure rehospitalization is defined as an unscheduled admission for a primary diagnosis of worsening heart failure lasting >24 h, supported by new/worsening symptoms and signs and intensification of heart-failure therapy. All-cause rehospitalization is any unscheduled inpatient admission meeting the same duration rule, irrespective of cause. Cardiovascular events include cardiovascular death, nonfatal myocardial infarction, nonfatal stroke, resuscitated cardiac arrest, malignant arrhythmia and heart-failure rehospitalization. A blinded clinical endpoint committee, composed of three cardiologists blinded to treatment allocation, will adjudicate events from source documents. Disagreements will be resolved by consensus or by a fourth senior adjudicator. Only committee-adjudicated events will be used in the primary analyses of rehospitalization and cardiovascular outcomes.

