# Long-term efficacy and impact on rehospitalization of Qishen granules in patients with hypertension and heart failure with reduced ejection fraction: a multicenter, randomized, double-blind, placebo-controlled trial protocol

**DOI:** 10.3389/fcvm.2026.1897966

**Published:** 2026-09-07

**Keywords:** Chinese medicine, clinical protocol, HFREF, hypertension, RCT - randomized controlled trial

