NYHA cardiac function classification serves as a widely accepted indicator for assessing impaired cardiac function (19, 20). Echocardiography accurately reflects ventricular remodeling and cardiac function status (21), making it one of our secondary outcome measures. Additionally, this study comprehensively evaluated patients’ living conditions, social quality, and physical changes. Therefore, the KCCQ and the Heart Failure Toxic Syndrome Quantification Scale were also considered as secondary outcome measures.

This study involves multiple participating institutions, making quality control one of our primary challenges. We established Standard Operating Procedures (SOP) and provided extensive training to all investigators/physicians prior to patient recruitment. Through initial, supplemental training, and ongoing review, we ensured proper execution of SOP to guarantee data collection quality. Furthermore, we prioritized patient communication to ensure all participants had a thorough understanding of the trial, enabling strict adherence to requirements and attendance at all scheduled appointments.

This study design strictly adheres to the CONSORT guidelines employing a multicenter, randomized, double-blind, placebo-controlled trial design to minimize bias (22). The sample size calculation is scientifically sound, with a follow-up period extending to 52 weeks, enabling thorough assessment of long-term efficacy and safety outcomes. Furthermore, we incorporated readmission rates as a late-stage follow-up indicator, directly linking to health economics metrics, thereby demonstrating strong clinical and practical significance. We anticipate this clinical trial will provide high-level evidence-based medical evidence for the application of traditional Chinese medicine in the field of hypertension-related heart failure.

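### All-cause rehospitalization is defined, but the week 26/52 collection sentence covers only heart-failure admissions and major cardiovascular events, and the event for each time-to-first-event analysis is not named

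*Protocol article*

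**What the plan says.** The title announces "Long-term efficacy and impact on rehospitalization of Qishen granules", and the abstract's Methods describe "follow-up assessments at weeks 26 and 52 to evaluate patient readmission rates and the occurrence of cardiovascular adverse events".

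Section 2.12.4 sets out the long-term follow-up:

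- **Data collected:** "investigators will collect the number and dates of heart-failure rehospitalizations and major cardiovascular events".
- **Sources:** "through scheduled contact, participant/family interview and review of hospital source records".
- **Heart-failure rehospitalization:** unscheduled, longer than 24 h, with worsening heart failure as primary diagnosis.
- **All-cause rehospitalization:** "All-cause rehospitalization is any unscheduled inpatient admission meeting the same duration rule, irrespective of cause".
- **Cardiovascular events:** "Cardiovascular events include cardiovascular death, nonfatal myocardial infarction, nonfatal stroke, resuscitated cardiac arrest, malignant arrhythmia and heart-failure rehospitalization".
- **Adjudication:** the primary analyses of rehospitalization and cardiovascular outcomes use only events confirmed by the blinded endpoint committee.

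Section 2.15 analyses time to first event with Kaplan–Meier curves, a log-rank test and Cox regression (hazard ratio with 95% confidence interval). It does not say whether the event is heart-failure rehospitalization, all-cause rehospitalization or the cardiovascular composite. For repeat events it states: "Event counts and recurrent rehospitalizations will be summarized descriptively by group".

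**The concern.** Section 2.12.4 defines one outcome more broadly than the data it tells sites to collect. Pneumonia, a fracture or a non-cardiac renal admission would count towards all-cause rehospitalization, but belongs to neither group of events that investigators are told to record. A later analysis plan cannot repair this, because it cannot analyse admissions that were never recorded. Recovering them afterwards from the 11 centres listed in section 2.2 is likely to be uneven.

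Deaths raise a related question. Only cardiovascular death is listed. A participant who dies of another cause needs a date of death, both for censoring and for treating death as a competing event, and section 2.12.4 does not ask for one.

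Two lesser matters concern the analysis. The number and dates of admissions are collected and the abstract speaks of readmission rates, yet no between-group estimate uses admissions after the first. If Kaplan–Meier is applied to heart-failure rehospitalization alone, death is treated as ordinary censoring and the curve overstates the risk of admission.

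**Working it through.** **1. Coverage of each outcome by the collection sentence (section 2.12.4)**

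| Event in weeks 0–52 | Needed for | In the collected categories? |
|---|---|---|
| Heart-failure admission > 24 h | HF, all-cause, CV composite | Yes |
| MI, stroke, resuscitated arrest, malignant arrhythmia | CV composite; all-cause if admitted | Yes |
| Other unscheduled admission > 24 h | All-cause | No |
| Cardiovascular death | CV composite; competing event | Yes |
| Non-cardiovascular death | Censoring date; competing event | Not listed |

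The third row is the contradiction and the fifth is the ambiguity.

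**2. What the stated sample size was built for (section 2.3)**

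Inputs: responder rates 53% and 33%, two-sided α = 0.05 (two-tailed per section 2.15), power 80%, dropout 15%. With unpooled variance:

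n = (0.53×0.47 + 0.33×0.67) × (1.960 + 0.842)² / 0.20² = 92.3, so 93 per arm; 93/0.85 = 109.4, so 110.

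The stated 110 per group reproduces. It concerns the 12-week NT-proBNP responder rate; the article gives no planning figure for rehospitalization. Everything below therefore rests on assumed rates.

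**3. Kaplan–Meier against cumulative incidence for heart-failure rehospitalization**

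The article puts five-year survival below 50%. Taking 50% and a constant hazard, d = −ln(0.5)/5 = 0.139 per year, which is 1 − 0.5^(1/5) = 12.9% mortality at one year. With an assumed heart-failure admission hazard h, independent of death:

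- Kaplan–Meier: 1 − exp(−h)
- Cumulative incidence: h/(h+d) × [1 − exp(−(h+d))]

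| h per year | Kaplan–Meier | Cum. incidence, d = 0.139 | Excess | Cum. incidence, d = 0.07 | Excess |
|---|---|---|---|---|---|
| 0.20 | 18.1% | 17.0% | 1.2 points | 17.5% | 0.60 points |
| 0.25 | 22.1% | 20.7% | 1.4 points | 21.4% | 0.73 points |
| 0.35 | 29.5% | 27.7% | 1.8 points | 28.6% | 0.95 points |

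The d = 0.07 columns assume about half the mortality. That is plausible because sections 2.5 and 2.6 select stable NYHA II–III patients up to age 75 and exclude those with severe heart failure and a life expectancy under six months.

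**4. What inference on recurrent admissions would add**

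Simulation with 110 per arm, one year of follow-up, and assumed values of 0.4 events per year in the control arm and gamma frailty variance 1:

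| Assumed rate ratio | Power, rate comparison with robust variance | Power, first event |
|---|---|---|
| 0.60 | about 44–45% | about 35–37% |
| 0.75 | about 19–20% | about 16% |

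The ranges are Monte Carlo variation between runs of 1,500 to 3,000 replicates. The gain is roughly 8 to 10 percentage points in the favourable case and 3 to 4 in the other. Power is low either way.

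**The case against.** The strongest reply is that one sentence is incomplete rather than that the outcome is unobtainable. Investigators must look at unscheduled admissions in general to decide which were for heart failure. Interviews and hospital records would bring the others to light, and case report form items are normally left to the full protocol. This lowers the likely harm but does not remove the contradiction: the sources are named as the means of collecting heart-failure and cardiovascular events, and nothing says that other admissions are recorded or sent for adjudication.

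A reader might infer that deaths from other causes are lost and that dead patients stay in the risk set. The article does not support that. Deaths must be identified before they can be classified as cardiovascular, family interview is a named source, section 2.12.3 grades adverse events up to fatal, and section 2.7 follows endpoint events after withdrawal. What remains is that non-cardiovascular death is not explicitly listed.

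A reader might also conclude that the rehospitalization question in the title goes unanswered. It does not: first heart-failure rehospitalization is collected, adjudicated and compared by log-rank and Cox. Summarizing recurrent events descriptively is a stated choice, not an error. The competing-risk point touches only the Kaplan–Meier display, in both arms; a Cox model that censors at death already gives the cause-specific hazard ratio.

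Finally, the Discussion's phrase "enabling thorough assessment of long-term efficacy and safety outcomes" might be set against safety visits that appear to end at week 12. Scheduled tests are at weeks 0, 4 and 12, but section 2.12.3 states no end to adverse event monitoring. Sizing a trial on its primary endpoint alone is normal. The wording of the title and Discussion changes no step of design or analysis.

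**Conclusion.** The mismatch inside section 2.12.4 is real and should be corrected while follow-up data can still be collected. As written, all-cause rehospitalization cannot be built reliably, and non-cardiovascular deaths are not explicitly part of the long-term dataset. This conclusion comes from comparing the text with itself and needs no assumed rate. How many admissions would be missed cannot be estimated from the article.

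The failure to name the event in section 2.15 is a smaller gap that compounds the first, since three candidate events are defined.

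The remaining two items are improvements, not corrections. The Kaplan–Meier excess is about 0.6 to 1.8 percentage points at 52 weeks, and recurrent-event inference adds about 3 to 10 percentage points of power. Both ranges depend on assumed event rates, mortality, effect size and frailty that the article does not give.

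**What to change.** **Section 2.12.4.** Have investigators record the number, dates and cause of every unscheduled admission lasting more than 24 h, and the date and cause of every death, from randomization to week 52. State that these go to the endpoint committee. Alternatively, delete the all-cause definition.

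**Section 2.15.** Name the event (heart-failure rehospitalization, all-cause rehospitalization or cardiovascular composite) for each time-to-first-event analysis.

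**Recommended additions in section 2.15.** Beside the descriptive summary of recurrent rehospitalizations, report a between-group rate ratio with 95% confidence interval, from a negative binomial model with a follow-up offset or a recurrent-event model with robust variance, labelled exploratory. Display heart-failure rehospitalization as cumulative incidence with death as a competing event. The Cox cause-specific hazard ratio can stay.

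**Cost.** A few case report form items at contacts already scheduled, some additional adjudication, and slightly more analysis. Sample size, visits and primary endpoint are unchanged.
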